### Intervention

The participants from outpatient departments will receive acupuncture treatments in the outpatient clinic of the acupuncture department three times per week for 4 weeks. The inpatients will receive acupuncture treatment three times per week at the time of hospitalization, and will then receive outpatient treatment three times per week for 2 weeks. In each treatment session, every patient will be placed in a separate quiet space and asked to wear an eye-patch. Each treatment session will be 20 min. The treatment course will last for 4 weeks, and the follow-up period will be 4 weeks. All participants will receive standard Western medicine therapy for stroke, limb function rehabilitation therapy, and clinical nursing in Shanghai Municipal Hospital of Traditional Chinese Medicine. To improve adherence to intervention protocols, all participants will receive intervention and assessments by telephone reservations, and be given some financial subsidies after follow-up.

Patients in both groups will be treated with stainless steel needles (0.25 × 25 mm and 0.30 × 40 mm; Wuxi Jiajian Medical Material Co., Ltd., Wuxi, China) at the same acupoints, including *Baihui* (DU20), *Shenting* (DU24), *Yintang* (EX-HN3), bilateral *Anmian* (EX-HN22), bilateral *Shenmen* (HT7), and bilateral *Sanyinjiao* (SP6). The acupuncturist will use 0.25 × 25-mm needles for acupoints DU20, DU24, EX-HN3 and HT7, and 0.30 × 40-mm needles for acupoints EX-HN22 and SP6 (Table 2).

**Table 2 Tab2:** Details of interventions

	Intervention group	Control group
Acupoints	DU20, DU24, EX-HN3, EX-HN22, HT7, SP6	DU20, DU24, EX-HN3, EX-HN22, HT7, SP6
Depth of needle insertion	DU20, DU24, EX-HN3: 10 mm	No needle insertion
	EX-HN22, SP6: 15 mm	
	HT7: 5 mm	
Needle retention time	20 min	20 min
Needle type	Stainless steel	Blunt stainless steel
	(0.25 × 25 mm or 0.30 × 4 0 mm; Wuxi Jiajian, Wuxi, China)	(0.25 × 25 mm or 0.30 × 40 mm; Wuxi Jiajian, Wuxi, China)
Frequency and duration of treatment sessions	Three times a week for the subsequent 4 weeks	Three times a week for the subsequent 4 weeks
Needle stimulation	*De-qi* sensation	Without *De-qi* sensation

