### Randomization

We plan to use the random block method. An independent researcher, who has no contact with any participant, will use SPSS version 23.0 software (SPSS Inc., Chicago, IL, USA) to generate a random number table to divide the eligible participants in a 1:1 ratio into the intervention group and the control group. The random allocation sequence will be generated in a block of 3. The researcher will then make random allocation cards and seal each card in an opaque envelope whose number is the same as the number on the card. According to the time order in which patients are asked to go to the hospital, another researcher will arrange the patients into different groups and inform the acupuncturists of the group assignment.

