### Blinding method

This is a single-blinded (patient-assessor-blinded) study. Participants will be asked to wear an eye-patch in a separate quiet space before treatment, and will remain blinded during the whole treatment. Except for the acupuncturists, all other researchers (including the statisticians, outcome assessors, and data analysts) will be blinded to the group assignment. We will attempt to validate the successful implementation of the blinding method. At first treatment, all patients will be told that the needling sensation that they are experiencing is the real sensation of acupuncture. In addition, all researchers will undergo training on the specifications of this RCT before commencement, and will strictly adhere to the separation principle of each department. The primary blinding method was successfully implemented by Lao et al. [24] in a trial to evaluate the efficacy of acupuncture treatment for postoperative oral surgery pain. We used this report as a reference to improve the design of our RCT and to ensure successful completion.

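### List order follows when patients are called in, under one small disclosed block, which leaves room for selection bias; and the statement that only the acupuncturists are unblinded contradicts the allocation procedure.

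*Protocol article*

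**What the plan says.** All from the Protocol article.

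- **List generation (Randomization).** "An independent researcher, who has no contact with any participant, will use SPSS version 23.0 software" to make the list and "divide the eligible participants in a 1:1 ratio into the intervention group and the control group". On block size: "The random allocation sequence will be generated in a block of 3".
- **Concealment device (Randomization).** The same researcher will make the cards and "seal each card in an opaque envelope whose number is the same as the number on the card".
- **Order and allocation (Randomization).** The order rule reads: "According to the time order in which patients are asked to go to the hospital, another researcher will arrange the patients into different groups". The second task of this person is to "inform the acupuncturists of the group assignment".
- **Blinding (Blinding method).** "Except for the acupuncturists, all other researchers (including the statisticians, outcome assessors, and data analysts) will be blinded to the group assignment". The section adds a general commitment to keep departments separate.
- **Timing (Recruitment; Table 1).** Eligibility is checked at the first visit. Consent is required before acupuncture. Table 1 puts consent and randomization in the same Week 0 column.
- **Booking (Intervention).** As an adherence measure, "all participants will receive intervention and assessments by telephone reservations".
- **Setting and analysis.** There is one centre, no stratification is stated, and 60 patients are planned. The primary outcome is change in the self-rated PSQI, and measurement data are compared by t test.

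**The concern.** Two things in the stated procedure look wrong.

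First, the rule that fixes a patient's place on the list is tied to when the patient is asked to come in. That is an action by staff. It is not a logged event, such as completed consent and baseline, that can no longer be moved. Under a single small disclosed block, past assignments reveal part of what comes next. Someone who knew them and could influence the call order could bring in likely improvers when real acupuncture was the better guess. Patients range from 2 weeks to 2 years after stroke, so prognosis may be partly visible beforehand. The arms would then differ before treatment, and the planned t test would count that difference as an effect of acupuncture. Blinding of patients does not protect against this.

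Second, the allocating researcher must know each assignment in order to pass it on, yet the blinding statement exempts only the acupuncturists.

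This is separate from the arithmetic point that a block of 3 cannot be 1:1 within itself. It needs its own action, because correcting only the arithmetic can make prediction easier.

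**Working it through.** **1. The plan's own figure.** 24 per group with 20% dropout: 24/(1 − 0.20) = 30 per group, 60 in total. This reproduces the stated 60, which is used below.

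**2. Predictability.** The observer knows the block size and all past assignments and makes the best guess at each position. Pure chance gives 50% correct and 0% certain. An odd block cannot be 1:1 within itself, so two readings are worked.

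*Reading A: blocks of 3, each split 2:1 or 1:2 at random* (six equally likely blocks).
- Position 1: 1/2.
- Position 2: 2/3. After an A, two of the three remaining blocks continue with B.
- Position 3: the first two match with probability 1/3, and the third is then certain. Otherwise it is even. So 1/3 × 1 + 2/3 × 1/2 = 2/3.
- Correct: (1/2 + 2/3 + 2/3)/3 = 0.611. Certain: (1/3)/3 = 0.111, about 7 of 60.

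*Reading B: 3 means three per arm, so a block of 6.*
- Best-guess probabilities by position: 0.5, 0.6, 0.6, 0.7, 0.7, 1.0. The sum is 4.1, and 4.1/6 = 0.683 correct.
- The expected length of the determined run at the end of a block is 6/4 = 1.5. Certain: 1.5/6 = 0.25, or 15 of 60.

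**3. What steering could do.** Assumed, since the documents give no figure: every informative guess is used, the patient's expected PSQI change moves by δ SD toward the guessed arm, and there is no shift when the guess is even. Acupuncture has no effect and there are 30 per arm. The spurious difference is about 2δ × (2 × share correct − 1):

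- Reading A, δ = 0.25: 2 × 0.25 × 0.222 = 0.11 SD.
- Reading B, δ = 0.25: 2 × 0.25 × 0.367 = 0.18 SD.

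The standard error is about √(2/30) = 0.258 SD. Simulated error of a nominal two-sided 5% t test (at least 6,000 trials per case where the simulation size is recorded):

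| Scheme | Correct | Certain | Error, δ = 0.25 | Error, δ = 0.5 |
|---|---|---|---|---|
| Reading A | 61% | 11% | about 7% | about 12% |
| Reading B | 68% | 25% | about 10% | about 25% |
| Fixed block of 4 | 71% | 33% | about 12% | 31–33% |
| Blocks of 4 and 6 varied at random, sizes hidden | 69% | 5.5% | 11–12% | 27–28% |
| One 30+30 list | 57% | 3% | 5–6% | 7–8% |

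In the varied-block row, the error rates come from guessing the arm that is behind in the running count, which needs no knowledge of block size. Varying the size removes most of the certainty but not the guessing. What matters is that whoever can influence order does not see past assignments.

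**4. The two sections side by side.** Randomization has a second researcher, who is not described as an acupuncturist, place patients and report the assignment onward. It also has a first researcher generate the list and make the cards. Both know assignments. Blinding method says that everyone except the acupuncturists is blinded. Both statements cannot hold.

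**The case against.** The strongest defence is that standard safeguards are present. The list is made by someone with no patient contact, and the cards lie in numbered opaque envelopes. A separate researcher is in charge of recruitment, and the departments are to be kept apart. Randomization applies to eligible patients, and Table 1 places history, PSQI, ISI and actigraphy in a baseline column before Week 0. Patients make the first telephone contact themselves, and the telephone reservations in the Intervention section concern people already in the trial.

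Much of this stands, and it limits the point in four ways.

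- A reader might infer that the allocator decides whom to call next. The text says only that allocation follows a time order, not who sets it.
- A reader might infer that the allocator could also assess outcomes. The blinding section rules that out, because assessors are to be blinded. Nor does the contradiction show that assessors or statisticians are unblinded.
- A reader might infer that randomization is cut loose from eligibility. It is not. What is open is the order of consent and randomization within Week 0, and the event that fixes list position.
- A larger figure follows if blocks alternate 2:1 and 1:2 (78% correct, 44% certain). No such scheme is documented, so it is not relied on here.

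What does not stand is that the envelopes settle the matter. They hide the next card, but they do not prevent inference from past cards. The separation commitment does not name the allocator, recruitment or booking. The ordering rule and the blinding statement are both written out, so this is not detail left to a fuller protocol.

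**Conclusion.** The point holds in limited form, as a change that should be made. The ordering rule leaves list position open to influence. With one small disclosed block, a person who sees past assignments guesses about 61% to 68% correctly and knows 11% to 25% for certain, depending on how the block of 3 is read. Whether anyone both knows past assignments and can influence order is not stated, so this is an opportunity for selection bias and not evidence of it. At an assumed 0.25 SD shift the type I error rises from 5% to about 7% to 10%. That is modest, and it rests wholly on the assumed shift and on steering at every informative guess.

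The contradiction over blinding is certain and needs no assumption: the allocating researcher and the list generator know assignments. It reaches no further than those two roles.

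**What to change.** 1. **Randomization, order.** Replace the call-order rule. The next numbered envelope goes to the next patient to complete eligibility check, signed consent and baseline assessment, and each patient is irrevocably logged before the envelope is opened.
2. **Randomization, roles.** State that whoever knows past assignments (allocator, generator, acupuncturists) takes no part in recruiting, eligibility decisions, booking the order of first visits, or assessing.
3. **Blinding method.** List the allocator and the generator as unblinded. Alternatively, have the acupuncturist, who is unblinded anyway, open the envelope at the first session, and add only the generator to the list.
4. **Unused envelopes.** When the block size is corrected, do not use a single disclosed size; a fixed 4 would give 71% correct and 33% certain. Do not rely on varied sizes alone either, since these still allow about 69% correct guessing by someone who sees past assignments. Item 2 carries the protection.
5. **Patients already randomized.** Recruitment began in July 2016, so report the rule used for them.

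The cost is a short amendment, a new list for the unused envelopes, and slightly stricter role separation among existing staff. No extra patients or procedures are needed.

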### Blinding method

This is a single-blinded (patient-assessor-blinded) study. Participants will be asked to wear an eye-patch in a separate quiet space before treatment, and will remain blinded during the whole treatment. Except for the acupuncturists, all other researchers (including the statisticians, outcome assessors, and data analysts) will be blinded to the group assignment. We will attempt to validate the successful implementation of the blinding method. At first treatment, all patients will be told that the needling sensation that they are experiencing is the real sensation of acupuncture. In addition, all researchers will undergo training on the specifications of this RCT before commencement, and will strictly adhere to the separation principle of each department. The primary blinding method was successfully implemented by Lao et al. [24] in a trial to evaluate the efficacy of acupuncture treatment for postoperative oral surgery pain. We used this report as a reference to improve the design of our RCT and to ensure successful completion.

### Safety assessment

Participants will be asked to report any adverse event or related information after acupuncture treatment. The detail of every adverse event will be measured by [name] and reported in the Case Report Form. Adverse events include any unfavorable or unintended signs, symptoms, or diseases occurring during the whole RCT.

### Statistical analysis

All data will be analyzed according to the ITT principle to reduce deviation. The Student’s *t* test will be used to compare differences in measurement data. The rank sum test will be used to deal with ranked data, and the chi-squared test will be used to analyze categorical data. Analyses will be performed with SPSS version 23.0 software (SPSS Inc., Chicago, IL, USA).

### Monitoring

To guarantee the quality of this RCT, it will be carried out by Shanghai Municipal Hospital of Traditional Chinese Medicine. We will promptly input data from this RCT on the ResMan website at http://www.chictr.org.cn/index.aspx. As the Data Monitoring Team to identify problems in the project, examine collected data, and control bias, The Clinical Research Center of Drugs of the Shanghai University of Traditional Chinese Medicine will have access to these interim results and make the final decision to terminate the trial. A qualified clinical trial expert will be invited to monitor this RCT.

### Clinical trial registration

We applied for registration of this RCT in the Chinese Clinical Trial Registry. This will reduce all kinds of bias in clinical research, increase the transparency of trials, ensure the high quality of clinical trials and test processes, and the credibility of results.

## Discussion

Acupuncture treatment has been widely used to reduce the symptoms of insomnia [25]. There is minimal theoretical research or clinical RCTs on acupuncture for insomnia following stroke. This RCT will investigate the effectiveness of acupuncture in reducing insomnia following stroke. We are attempting to conduct a clinical RCT with adequate design and few deficits. We designed the sham acupuncture method without needle insertion to assess the specific effects of acupuncture rather than its placebo effect for treating insomnia following stroke. Furthermore, in contrast to the subjective assessments made in most trials, we will use actigraphy in our RCT to objectively assess the physiological changes in patients with insomnia. We will use the ITT principle to handle statistical data to reduce deviation of the RCT.

There are some inevitable limitations in this RCT. For example, it is hard to make the RCT double-blinded. The participants, the assessor, and the statistical expert will be blinded to the group assignment in this RCT; however, it will be impossible to blind the acupuncturist. This RCT is also restricted to a single-center hospital. Furthermore, although actigraphy is suitable for measuring nocturnal restlessness, it cannot differentiate between sleep stages or score rapid eye movement sleep, which may have helped to explain the mechanism of acupuncture for treating insomnia following stroke. In further studies, we may consider a multicenter clinical trial, using polysomnography as an assessment method.

### Trial status

We started recruiting participants in July 2016.

## Abbreviations

CBT: Cognitive behavioral therapy
HADS: Hospital Anxiety and Depression Scale
ISI: Insomnia Severity Index
ITT: Intention-to-treat
NIHSS: National Institutes of Health Stroke Scale
PSQI: Pittsburgh Sleep Quality Index
RCT: Randomized controlled trial
SD: Sleep disorders
SE: Sleep efficacy
SS-QOL: Stroke-Specific Quality of Life
TST: Total sleep time
